### Secondary outcome measures

 Correlations among imaging parameters Correlation coefficients between *f* and corresponding CBF values, and between *D* derived from the biexponential model and corresponding ADC values derived from the monoexponential model, will be calculated. It is hypothesized that both sets of correlations will be significant.

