**Methods:**

Patients that recently received a histopathological diagnosis of GBM at our hospital are eligible for enrollment. The patients selected will receive standard concurrent chemoradiotherapy and adjuvant temozolomide after surgery, and then will undergo conventional MRI, IVIM-DWI, 3D-ASL, and contrast-enhanced MRI. The quantitative parameters, ADC, *D*, *D**, *f*, and CBF, will be estimated for newly developed enhanced lesions. Further comparisons will be made with unpaired *t*-tests to evaluate parameter performance in differentiating true progression from pseudoprogression, while receiver-operating characteristic (ROC) analyses will determine the optimal thresholds, as well as sensitivity and specificity. Finally, relationships between these parameters will be assessed with Pearson’s correlation and partial correlation analyses.

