### Sample size calculation and statistics

A sample size calculation was performed with reference to a previous study that had a sensitivity of 71.0% and a specificity of 75.0% [16]. With a permissible error of 0.1 and an alpha significance level of 0.05, a sample size of 50 patients per group was enough to get satisfying statistic power.

Numerical variables will be expressed as the mean ± standard deviation (SD). Student’s *t*-test will be used to assess significant differences in the above mentioned parameters between the true tumor progression and the pseudoprogression cases. Receiver operating characteristic (ROC) analyses will determine corresponding specificity, sensitivity and cutoff points for differentiating true tumor progression from pseudoprogression based on ADC, *D*, *D**, *f*, and CBF values. Associations between *f*, *D*, and corresponding CBF and ADC will be assessed with Pearson’s correlation and partial correlation analyses, respectively. SPSS 17.0 software (SPSS Inc, Chicago, IL, USA) will be used for all statistical analyses and *p* < 0.05 indicate statistical significance.

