### Primary outcome measure

 Differences in diffusion-related parameters between true tumor progression and pseudoprogression according to the different fitting model
*D* and ADC will be derived from biexponential and monoexponential models, respectively. We hypothesized that true tumor progression and pseudoprogression can be distinguished based on these two values and true tumor progression can exhibit significantly lower mean *D* and ADC values compared with pseudoprogression. In addition, we hypothesized that *D*, which separates perfusion effects, will be a more promising parameter in distinguishing true tumor progression from pseudoprogression compared with ADC which can be compromised by perfusion. Differences in perfusion-related parameters between true progression and pseudoprogression Data regarding *D**, *f*, and CBF will be summarized. We hypothesized that *D**, *f*, and CBF will significantly differ between true tumor progression and pseudoprogression and Mean D*, f, and CBF values will be signifcantly lower for pseudoprogression than for true progression. Diagnostic Performance of the IVIM and 3D-ASL Parameters Receiver operating characteristic (ROC) analyses will determine corresponding cutoff points for differentiating true tumor progression from pseudoprogression based on ADC, *D*, *D**, *f*, and CBF values. In addition, sensitivity, specificity, and area under curve (AUC) for identifying true progression will be calculated in each case when pseudoprogression is differentiated. We will make a comparison among all the IVIM and 3D-ASL parameters to identify which has the best sensitivity/specificity with regards to early diagnosis. Establishment of Clinical prediction modelSingle factor analysis will show which covariates affect the judgment of newly developed enhanced or enlarged enhanced lesions, such as age, gender, radiation dose, karnofsky performance score, lesion region and imaging characteristics. A logistic regression equation will be performed to identify those covariates, IVIM and 3D-ASL parameters that contribute to the diagnostic differentiation between true progression and pseudoprogression.

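### The f–CBF correlation has no stated adjustment for diagnosis, so a pooled Pearson test could partly restate the group difference already tested as a primary outcome

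*Protocol article*

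**What the plan says.** Three parts of the protocol article bear on this.

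- **Secondary outcome measures** plans "Correlation coefficients between *f* and corresponding CBF values, and between *D* derived from the biexponential model and corresponding ADC values", and adds: "It is hypothesized that both sets of correlations will be significant". Neither sentence mentions diagnosis group.
- **Sample size calculation and statistics** names the methods. The associations of f and D with "corresponding CBF and ADC will be assessed with Pearson’s correlation and partial correlation analyses, respectively". The Abstract (Methods) has a shorter form without the last word: "relationships between these parameters will be assessed with Pearson’s correlation and partial correlation analyses". None of these places says what is held fixed in the partial correlation.
- **Primary outcome measure** states the expected direction for the perfusion measures: mean f "and CBF values will be signifcantly lower for pseudoprogression than for true progression".

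The statistics section sets significance at p < 0.05 and does not say whether tests are one- or two-sided. It plans 50 patients per group.

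**The concern.** Taken in order, *respectively* pairs f–CBF with plain Pearson correlation and D–ADC with partial correlation. On that reading, the f–CBF coefficient is computed over a sample made up of two groups whose means are expected to move together on both measures. Pooling such groups produces a positive correlation by itself, even when the two measures are unrelated among patients with the same diagnosis.

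What is at stake is how a secondary result is read. A significant pooled coefficient could be taken as showing that f follows CBF from lesion to lesion, when it may largely repeat the group contrast that the primary outcome already tests. The primary comparisons, ROC analyses and cutoffs are not affected.

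**Working it through.** The article gives no expected correlation, so there is no planned figure to reproduce. The check asks how often a pooled test is significant when f and CBF have zero correlation within each group.

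**Inputs from the article**
- 50 per group, so n = 100; p < 0.05 (Sample size calculation and statistics).
- Planning sensitivity 71% and specificity 75% (same section). The imaging parameter they belong to is not named there.
- Pseudoprogression in 20–30% of enlarging lesions (Background). A 75/25 split is used as the unbalanced case.
- Same direction of shift for f and CBF (Primary outcome measure).

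**Assumptions**
- Normal data, equal unit SDs, the same standardised gap d for f and CBF, and two-sided tests. The article gives no gap or SD for either measure, so a range of d is shown.

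**Reference values for d**
- 80% t-test power at 50 per group: (1.960 + 0.842) × √(2/50) = 0.56.
- 90% power: (1.960 + 1.282) × √(2/50) = 0.65.
- Planning accuracy, equal-variance binormal model: z(0.71) + z(0.75) = 0.553 + 0.674 = 1.23.

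**Correlation created by pooling.** With share q in one group, r = q(1−q)d² / (1 + q(1−q)d²).
- d = 1.0, q = 0.5: 0.25 / 1.25 = 0.20.
- d = 1.23, q = 0.5: 0.25 × 1.508 = 0.377, and 0.377 / 1.377 = 0.27.
- d = 1.23, q = 0.75: 0.1875 × 1.508 = 0.283, and 0.283 / 1.283 = 0.22.

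At n = 100 the critical value is t / √(98 + t²) with t = 1.984, which is 0.197.

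**Chance of p < 0.05 for the pooled Pearson test** (20,000 simulated trials per row, n = 100, zero within-group correlation):

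| Gap d, both measures | Pooled r, 50/50 | Significant, 50/50 | Pooled r, 75/25 | Significant, 75/25 |
|---|---|---|---|---|
| 0.56 | 0.07 | 11% | 0.06 | 9% |
| 0.65 | 0.10 | 16% | not run | not run |
| 0.8 | 0.14 | 28% | 0.11 | 19% |
| 1.0 | 0.20 | 53% | 0.16 | 35% |
| 1.23 | 0.27 | 82% | 0.22 | 61% |
| 1.5 | 0.36 | 97% | 0.30 | 88% |

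Simulation error is at most √(0.25/20,000) = 0.35 percentage points per entry. The chance passes one half at about d = 1.0 with equal groups and d = 1.14 with a 75/25 split.

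**After adjustment.** The partial correlation given diagnosis was significant in 4.6–5.2% of trials at every gap and split tried, from d = 0 to 2.0. The nominal 5% is restored.

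**The case against.** Four points can be made on the other side.

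1. **Pooling is not stated.** The article nowhere says that the f–CBF coefficient ignores diagnosis. *Respectively* may only match f to CBF and D to ADC, with both methods meant for both pairs, and the Abstract's wording supports that. This stands: a reader might infer that the plan commits to an unadjusted test for f–CBF, and the text does not go that far. Still, no controlling variable is named on either reading, so adjustment for diagnosis is neither planned nor excluded.

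2. **A spurious result need not be likely.** A reader might infer that expecting both measures to differ makes a significant pooled correlation probable in any case. It does not. The primary hypothesis can be met with good power at gaps of 0.56–0.65, where the chance is 11–16%. The 1.23 figure comes from one earlier study's accuracy and is applied here to both measures by assumption. This also stands.

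3. **A pooled correlation is a legitimate quantity.** Whether two perfusion measures move together across all enhancing lesions is a fair question, and differences by diagnosis are part of that variation. This stands too: the pooled coefficient is not wrong and should be reported. It answers a different question from the within-diagnosis correlation, and the article does not say which is meant.

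4. **A condensed article leaves such detail to a fuller document.** In part. Naming a control variable could well be left there. But the article does assign the methods and states a significance hypothesis, so the ambiguity lies in what it chose to specify.

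**Conclusion.** The point holds as a matter of specification and interpretation. The plan does not say that the f–CBF correlation is assessed within, or adjusted for, diagnosis, while it expects both measures to shift the same way between the groups. If the test is pooled, its chance of significance under zero within-group correlation exceeds 5%. The excess is modest at gaps just large enough for the planned t-tests. It is large if both measures discriminate about as well as the planning accuracy: 82% with equal groups, 61% at 75/25. The problem grows as the primary hypothesis succeeds.

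These sizes rest on the assumed gaps, normality, equal SDs and two-sided testing. The documents do not show that a misleading result is probable, or that pooled analysis was definitely chosen. The consequence is confined to a secondary outcome.

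**What to change.** In the statistics section:

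- State which pair (f–CBF, D–ADC) receives Pearson correlation, partial correlation, or both.
- Name diagnosis group (true progression or pseudoprogression) as the variable held fixed in the f–CBF partial correlation.
- Report that partial r with a 95% CI, and the two within-group correlations, beside the pooled Pearson r.
- Base any statement that f tracks CBF beyond the group difference on the adjusted result.

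**Cost.** A sentence or two, no new data, and one degree of freedom. The within-group estimates will be less precise. By Fisher's z, the 95% limits around r = 0 are ±tanh(1.96/√96) = ±0.20 for the partial r at n = 100, ±tanh(1.96/√47) = ±0.28 for a group of 50, and ±tanh(1.96/√22) = ±0.40 for a group of 25. If pseudoprogression cases are few, that group's correlation can only be descriptive.

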## Discussion

In patients with GBM after concurrent chemoradiotherapy, it is important to differentiate pseudoprogression from true progression to choose appropriate treatment and predict prognosis. In both situations, conventional MRI usually shows enhanced lesion with or without mass effect, so it cannot be conclusive. Few studies have examined the combination of IVIM and 3D-ASL imaging for distinguishing true progression from pseudoprogression of GBM, The current study attempts to validate perfusion and diffusion parameters derived from IVIM and 3D-ASL to determine whether an enlarged contrast-enhanced lesion was caused by true progression or by pseudoprogression. Advantages and disadvantages of this study are discussed below.

Compared to recently published studies in gliomas [15, 25], more and higher b values are used in our study, as more b values in segment of low b values can improve the accuracy of the pseudodiffusion, while higher b values can better eliminate the perfusion-related diffusion; thus it can in turn generate a more realistic molecular diffusion coefficient value. Perfusion imaging of brain tumors, which mainly includes DSC-MR perfusion techniques, has been used for the diagnosis of glioma recurrence and radiation necrosis [26–28]. However, the use of intravenous contrast media is a major limitation in the routine clinical application of this method, since contrast media extravasation can result in a decreased rCBV for high-grade tumors. The 3D-ASL is one submethod of ASL. It had been widely used in gliomas grading and had reliable results with DSC. In this technique, the contrast agent used is labeled arterial blood water proximal to the brain. Without intravenous contrast media, 3D-ASL imaging could be particularly relevant for the long-term follow-up of gliomas following radiation, including those with renal insufficiency or severe allergies. Several reports [26–28] have suggested that combining information derived from different techniques increases diagnostic performance not only for the identifcation of brain tumors but also for assessing the response to treatment. Because each parameter can show different aspects of tumor biology, the combination of parameters may have added value compared with single-parameter measurements.

We are expecting that combination of IVIM-DWI and 3D-ASL imaging has an acceptable accuracy in differentiating true progression from pseudoprogression However, there are several limitations of our study. First, patient recruiting is difficult. Second, manual ROI measurements that encompassed the entire lesion and targeted the areas of maximal abnormality is used to measure the parameters rather than a pixel-to-pixel method. This method may not reflect the intraregional tumor heterogeneity. However, these techniques are rapid, reproducible, simple, and are commonly used in clinical practice. Third, pathologic sampling regions lacks strict pathologic correlation of the image-based segmentation with surgical specimens, as shown by Hu et al. [10]. However, in clinical practice, such quantitative correlation is very difficult to achieve.

## Abbreviations

3D-ASL: Three-dimensional arterial spin labeling imaging
ADC: Apparent diffusion coefficient
AUC: Area under curve
CBF: Cerebral blood flow
*D**: Fast diffusion coefficient
*D*: Slow diffusion coefficient
DSC: Dynamic susceptibility-weighted contrast-enhanced
*f*: Perfusion fraction
FA: Fractional anisotropy
FOV: Field of view
FSE: Fast spin echo
GBM: Glioblastoma multiforme
IVIM-DWI: Intravoxel incoherent motion diffusion-weighted imaging
MRI: Magnetic resonance imaging
NEX: Number of excitations
ROC: Receiver-operating characteristic
TMZ: Temozolomide
SD: Standard deviation
TE: Echo time
TR: Repetition time
